| Type of Participants to be Studied and Justification | 
Healthy adults aged 18-75 years who do not have active conditions that require investigation or a change in treatment, and whose risk of exposure to SARS-CoV-2 is similar to the general population.
 
The upper age limit will be 45 years for the dose escalation and dose evaluation as this is a first in human study, and there is greater variability of immune responses in those aged over 45 years respectively. In order to accurately assess the immune responses, individuals with no evidence of natural infection will be enrolled. The sample size calculation for the first dose evaluation part of this study is based on testing the slope co-
                                                                                                                                                                                                                                                                                                                                                                                                                                                                                                                                                                                                                                                                                |

| SUMMARY INFORMATION TYPE            | SUMMARY DETAILS                                                                                                                                                                                                                                                                                                                                                                                                                                                                                                                                                                                                                                                                                                                                                                                                                                                                                                                            |

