|               |                                               | 10                 | 10                 |             |                                      | 20  |
| Total Group B |                                               |                    |                    |             |                                      | 165 |
| C             | Expanded safety
evaluation                 | 1                  | 1, 2.5, 5 or
10 | 18-75       | Collaborating
centres             | 222 |
| Total Group C |                                               |                    |                    |             |                                      | 222 |
| Total         |                                               |                    |                    |             |                                      | 414 |

**Figure 1: Trial Entry through the First Dose Evaluation Cohort (Groups A1 and B1) and Expanded Safety First Dose (Group C)**

[figure not shown]

**Figure 2: Trial Entry through the Second Dose Escalation (Group A2) and Evaluation (Group B2) and Second Dose in Expanded Safety group (Group C)**

[figure not shown]

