### 1.5.3 EXPANDED SAFETY EVALUATION

Provided there are nothing worse than transient Grade 3 reactions in the safety data collected to Day 7 (minimum) from the first 42 participants to receive one vaccination at 1 µg, further centres will be able to start injections, accumulating data in at least 200 individuals for the expanded safety evaluation of the 1 µg dose at Week 0. This will inform the safety of lower doses and is the most efficient way to proceed prior to review of immune responses.

The restriction on upper age of 45 years will be removed from the database and participants up to age 75 years will be eligible for enrolment in the expanded safety evaluation in order to evaluate immune responses across a broader age range.

At any point during the trial, persistent Grade 3 reactions or any serious adverse reactions will be immediately reported to the Trial Steering Committee (TSC). If there are two participants with persistent Grade 3 reactions, or one with a serious adverse reaction, in the first 20, vaccinations will be paused in all participants and the TSC will be asked to review the accumulated safety data and make a recommendation. If vaccinations are paused in all participants, a substantial amendment will be submitted to the competent authorities. Likewise, approval from the competent authorities is needed before the study can be resumed.

Although the original intention was for participants in the expanded safety evaluation to receive a 1 µg dose at both the first and second vaccinations, the TSC recommended that a higher, and we hope more immunogenic, dose be given at the second vaccination. We will proceed with 10 µg, provided this is sufficiently well tolerated in the second dose escalation/evaluation. The TSC agreed that we should assess the Day 7 (minimum) safety data from 20 (minimum) participants at each dose level in the second dose escalation/evaluation cohort, before asking the TSC to recommend which dose to use for the second vaccination of participants in the expanded safety evaluation. We believe this decision will be made in time for vaccinations at Week 14 of the participants' schedule. Alternatively, participants can elect to receive the 1 µg dose at Week 4, as originally planned.

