### 1.5.4 RATIONALE FOR CHOICE OF TRIAL POPULATION

First-in-human dosing for vaccine candidates is typically in healthy young adult populations as these individuals generate the most robust responses. However, it will be important to demonstrate immunogenicity in those most at risk of severe disease. As this risk increases with age, the upper age limit for the expanded safety evaluation is 75 years, recognising that government guidance on strict social distancing of the over 70 may make it difficult for participants over 70 years old to attend trial sites. All participants will provide samples for immunogenicity assessment, including measurement of titres of serum binding and neutralising antibodies, induction of high levels of which is believed to be essential for an effective vaccine. Thus we will be able to confirm immunogenicity of the vaccine in older participants.

Both male and female participants will be included and trial sites will attempt to keep an equal proportion, although the priority will be to ensure timely accrual to the trial.

In order to study the safety and immunogenicity of LNP-nCoVsaRNA vaccine in individuals with a history of SARS-CoV-2 infection, one investigator site (at St Mary's Hospital, London) will preferentially enrol participants known to have infection-induced SARS-CoV-2 antibodies prior to enrolment. The site's enrolment target is 30 participants.

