#### 3.1 PARTICIPANT INCLUSION CRITERIA

1. Healthy adults from the following age ranges:
  - a. For the dose escalation and evaluation, aged 18-45 years on the day of screening
  - b. For the expanded safety evaluation, aged 18-75 years on the day of screening
2. At similar risk of acquiring SARS-CoV-2 infection to the general population
3. Willing and able to provide written informed consent
4. If female and of childbearingi potential, willing to use a highly effective methodii of contraception from screening until 18 weeksiv after last injection
5. If male and not sterilised, willing to avoid impregnating female partnersiii from screening until 18 weeksiv after last injection
6. Willing to avoid all other vaccines from within 4 weeks before the first injection through to 4 weeks after the second injectionv
7. Willing and able to comply with visit schedule, complete online diaries and provide samples
8. Willing to grant authorised persons access to his/her trial-related medical record and GP records either directly or indirectly

i A woman will be considered of childbearing potential following menarche and until becoming post-menopausal (no menses for 12 months without an alternative medical cause) unless permanently sterile. Permanent sterilisation methods include hysterectomy, bilateral salpingectomy and bilateral oophorectomy. A post-menopausal state is defined as no menses for 12 months without an alternative medical cause.

ii The following methods are considered highly effective:

- combined (estrogen and progestogen containing) hormonal contraception associated with inhibition of ovulation – oral, intravaginal or transdermal;
- progestogen-only hormonal contraception associated with inhibition of ovulation – oral, injectable or implantable
- intrauterine device (IUD);
- intrauterine hormone-releasing system (IUS);
- bilateral tubal occlusion;
- vasectomised partner, where the vasectomised partner has received medical assessment of the surgical success; and
- sexual abstinence, defined as refraining from heterosexual intercourse – must be the preferred and usual lifestyle of the participant.

iii Through the use of condoms or sexual abstinence (see definition in footnote ii above)

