## 9.5 ANALYSIS PLAN

A full analysis plan will be provided in a separate Statistical Analysis Plan.

Primary safety analyses will be based on all participants who receive at least one dose of vaccine. Safety endpoints will be compared between the different dose groups. The frequency of adverse events will be tabulated by grade and MedDRA System Organ Class and treatment group, and MedDRA Preferred Term and treatment group. Groups will be compared using Fisher's exact test in terms of the proportion ever experiencing an event in each MedDRA System Organ Class.

Primary analyses of immunological responses at 6 weeks will be based on all participants who receive both the initial vaccination and the booster at 4 weeks. These analyses will exclude participants who are identified as COVID-19 seropositive at baseline (either retrospectively, or those enrolled at the St Mary's Hospital site with known previous SARS-CoV-2 infection). Data will also be censored on participants who acquire SARS-CoV-2 infection (virologically-confirmed) during follow-up or who receive an authorised COVID-19 vaccine.

Immunological responses at all time-points will be compared between the younger and older age groups using cross-sectional analyses and longitudinal multilevel models.

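### Section 9.5 words the age analysis as a younger/older comparison; for a roughly linear trend over evenly spread ages this gives up about a quarter of the information that continuous age would keep

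*Protocol*

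**What the plan says.** Section 9.5 of the protocol gives one sentence on age: "Immunological responses at all time-points will be compared between the younger and older age groups using cross-sectional analyses and longitudinal multilevel models". It states no cut-point, mentions no continuous age term and does not restrict the comparison to Group C. The same section says "A full analysis plan will be provided in a separate Statistical Analysis Plan".

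The cohorts differ in age by design. Section 3.1 sets the limits: "For the dose escalation and evaluation, aged 18-45 years on the day of screening" and "For the expanded safety evaluation, aged 18-75 years on the day of screening". Table 1 gives 222 participants in Group C. Section 1.5.3 explains the removal of the upper limit of 45: "in order to evaluate immune responses across a broader age range". Section 1.5.4 describes the risk of severe disease as rising with age and concludes "Thus we will be able to confirm immunogenicity of the vaccine in older participants".

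On where younger ends and older begins, the Summary of Trial offers an immunological reason for the limit of 45: "there is greater variability of immune responses in those aged over 45 years respectively". It then refers to the expanded safety evaluation as the part that brings in the older age group. Together these make 45 the natural cut.

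The protocol gives no age distribution for Group C, no expected shape for the relation of response to age, and no power for the age comparison.

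**The concern.** Group C is recruited over a continuous span of 57 years, and the protocol's own reasoning about risk is a gradient. A two-group contrast treats a 46-year-old and a 75-year-old as alike and a 45-year-old and a 46-year-old as different. When the response changes steadily with age, that discards the variation in age within each group, and the result depends on where the cut falls.

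The sentence in 9.5 is more than silence to be filled later, because it states the form of the comparison. An analysis plan that follows it literally would start from the split. What is at stake is the chance of seeing a real decline in response with age, in the only cohort that enrols people over 45. For dose, section 9.3 already does the more efficient thing: it tests a regression slope in the first cohort and expects non-linearity over the wider range.

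**Working it through.** **The plan's own figures.** The only immunogenicity power in the protocol is for the dose slope (section 9.3: 35 per dose, SD 1.5 on the log10 IC50 scale, two-sided 0.05). With doses coded 0, 1, 2, Sxx = 35 × (1 + 0 + 1) = 70, and the noncentrality is d × √70 / 1.5 for an adjacent-dose difference d. With a noncentral t on 103 df, d = 0.7, 0.6, 0.5 and 0.4 give 97.2%, 91.2%, 78.9% and 59.9%. The protocol states 97%, 91%, 79% and 59%, so its figures reproduce. The SD of 1.5 is carried over below.

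**Information kept by a split.** If the true trend in age is linear, the share of information kept by a two-group split at c is the squared correlation between age and the indicator of age above c. For ages uniform over a span L, the two group means differ by L/2, so the between-group variance is p(1−p)L²/4, where p is the share below the cut. Dividing by the total variance L²/12 gives

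efficiency = 3p(1−p).

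With ages uniform on 18-75 (an assumption), p = (c − 18)/57.

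**Power.** Size the slope so that continuous age has 80% power: b = (1.960 + 0.842) × 1.5 / (√222 × 57/√12) = 0.0171, or 0.17 log10 per 10 years. The split then has power Φ(√efficiency × 2.802 − 1.960).

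| Cut | p | Efficiency | Loss | Equivalent N of 222 | Power |
|---|---|---|---|---|---|
| 45 | 0.474 | 0.748 | 25% | 166 | 68% |
| 46.5 (median) | 0.500 | 0.750 | 25% | 166.5 | 68% |
| 55 | 0.649 | 0.683 | 32% | 152 | 64% |
| 65 | 0.825 | 0.434 | 57% | 96 | 45% |

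The loss does not depend on N. With 192 in place of 222 (removing the enrolment target of 30 at the site that preferentially enrols antibody-positive people), a larger slope of 0.184 per 10 years is needed for 80%, and the split at 45 again has 68%.

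**Other age mixes, linear trend, cut at 45 (simulated).** Truncated normal with mean 46.5 and SD 14: loss 33%. Skewed young: 30%. U-shaped: 19%. Bimodal at 30 and 60: 10% with SD 5 and 19% with SD 8.

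**Other shapes, uniform ages, cut at 45.** Share of the age signal captured by each analysis:

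| True shape | Split at 45 | Linear term |
|---|---|---|
| Step at 45 | 100% | 75% |
| Flat, falling over 40-50, then flat | 94% | 83% |
| Flat, falling over 35-55, then flat | 89% | 90% |
| Change beginning at 45 | 59% | 82% |
| Linear throughout | 75% | 100% |

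**Adding the 1 µg participants of A1 and B1.** These are 7 + 35 = 42 people aged 18-45. With the same slope and uniform ages within each cohort, the split at 45 on all 264 has 75% power and a continuous term on the same 264 has 86%.

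**The case against.** The strongest reply is that this is a matter for the separate analysis plan. Cut-points and the form of a covariate in a multilevel model are commonly left there, and nothing in 9.5 forbids a continuous age term. The absence of a cut-point is therefore no fault. What remains is that the sentence names a form, and the form is the less efficient one for a gradual trend.

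A reader might infer that the split discards at least 25% of the information whatever happens. The documents do not support that. The figure needs a linear trend and a roughly even age mix (or one peaked in the middle, where the loss is larger), and the protocol states neither. Recruitment clustered at the two ends would bring the loss to 10-19%, although nothing in the protocol plans for that and section 1.5.4 expects difficulty in getting people over 70 to sites.

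A reader might also infer that the split loses against a linear term under any gradual decline. It does not: a fall confined to ages 40-50 favours the split. This is why a straight line alone is not the remedy and curvature must be allowed for. Nor are the losses at cuts of 55 and 65 forecasts, since the text points to 45.

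Pooling with the 1 µg participants of A1 and B1 does raise the power of the split to 75%, but the continuous term gains as well and stays ahead.

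Finally, age appears in none of the immunogenicity objectives, and responses observed in older people bear directly on whether the vaccine is immunogenic in them, with or without an age slope. That limits the importance of the point. It does not make the split the better analysis.

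**Conclusion.** The point holds as a conditional one. With ages roughly uniform over 18-75 and a roughly linear trend, a split at 45 loses about 25% of the information on the age trend: 222 participants do the work of about 166, and 80% power becomes about 68%. Later cuts lose more. The loss shrinks to 10-19% if ages cluster at the extremes and vanishes if the true change is a step at the cut. The power figures also assume one SD of 1.5 at all ages, which sits uneasily with the protocol's remark on greater variability above 45, and a single cross-section rather than repeated measures.

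It would go too far to conclude that the trial is underpowered or that a stated figure is in error. The age comparison is secondary, no sample size rests on it, and the powers in section 9.3 reproduce. It is a worthwhile and inexpensive improvement.

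**What to change.** In section 9.5, and in the analysis plan that follows from it, state that log10 titre will be modelled on age as a continuous variable in both the cross-sectional and the multilevel analyses, with a restricted cubic spline to allow for curvature. Fit the model within Group C, and at time-points after the boost account for second-dose level and interval, which vary within that group. The participants aged 18-45 given 1 µg in A1 and B1 may be added where dose and schedule match. Keep the younger/older comparison, with the cut stated as 45 years, as a descriptive summary.

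The cost is a sentence or two of text. No new data are needed, because eligibility already requires age at screening. The downsides are small: a slope or curve is slightly harder to present than two means, and a true step at 45 would be found slightly better by the split.

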## 10 REGULATORY & ETHICAL ISSUES

### 10.1 COMPLIANCE

#### 10.1.1 REGULATORY COMPLIANCE

The trial will be conducted in compliance with the approved protocol, the Declaration of Helsinki 1996, the principles of Good Clinical Practice (GCP) as laid down by the ICH topic E6 (R2), Commission Clinical Trials Directive 2005/28/EC\* with the implementation in national legislation in the UK by Statutory Instrument 2004/1031 and subsequent amendments, General Data Protection Regulation and the UK Data Protection Act 2018, and the UK Policy Framework for Health and Social Care Research.

\*Until the Clinical Trials Regulation EU No 536/2014 becomes applicable, the trial will be conducted in accordance with the Clinical Trials Directive as implemented in the UK statutory instrument. When the directive is repealed on the day of entry into application of the Clinical Trial Regulation the trial will work towards implementation of the Regulation (536/2014) following any transition period.

#### 10.1.2 SITE COMPLIANCE

An agreement will be in place between the site and the CTU, setting out respective roles and responsibilities (see [Section 12 - Finance](#)).

The site should inform CTU as soon as they are aware of a possible serious breach of compliance, so that the CTU can report this breach if necessary within 7 days as per the UK regulatory requirements. For the purposes of this regulation, a 'serious breach' is one that is likely to affect to a significant degree:

- The safety or physical or mental integrity of the subjects in the trial, or
- The scientific value of the trial

#### 10.1.3 DATA COLLECTION & RETENTION

Worksheets, clinical notes and administrative documentation should be kept in a secure location (for example, locked filing cabinets in a room with restricted access) and held for a minimum of 25 years after the end of the trial. During this period, all data should be accessible, with suitable notice, to the competent or equivalent authorities, the Sponsor, and other relevant parties in accordance with the applicable regulations. The data may be subject to an audit by the competent authorities. Medical files of trial participants should be retained in accordance with the maximum period of time permitted by the hospital, institution or private practice.

Note: EU Clinical Trial Regulation 536/2014 states the following:

“Unless other Union law requires archiving for a longer period, the sponsor and the investigator shall archive the content of the clinical trial master file for at least 25 years after the end of the clinical trial. However, the medical files of subjects shall be archived in accordance with national law.”

### 10.2 ETHICAL CONDUCT

#### 10.2.1 ETHICAL CONSIDERATIONS

Please see [Section 8.1](#) for the risks identified for the safety and rights of participants, which include the risk of unexpected serious adverse reactions and the need to collect and hold personal data. The main ethical considerations, and mitigations, are described below:

- The trial is in healthy volunteers so all visits required by the trial are in addition to their usual lifestyle and therefore are a burden. Vaccine trials are (necessarily) relatively lengthy, so

participation represents a significant time commitment. The requirement to attend all study visits within specified windows might be an inconvenience to some volunteers if their circumstances change during the trial. Furthermore, attending visits may increase the risk to participants of SAR-CoV-2 infection above that if the individual had stayed at home. Participants will be instructed to follow national guidance for the reduction of risk appropriate to their demographic.

- Participants may be overly motivated to participate based on their desire to gain protection from COVID-19. Great care will be taken to inform participants of the risks and benefits in taking part in this study, and to ensure that they continue to follow national guidance for the reduction of risk appropriate to their demographic.
- Fainting may occur around the time of vaccine injection or blood sampling, particularly in those who strongly dislike needles. To minimise this risk, participants will be asked to recline or lie down during those procedures.
- Blood tests can sometimes cause bruising and soreness of the arms or, very rarely, a blockage of a vein or a small nerve injury which can cause numbness and pain.
- The vaccine has not been tested for safety in pregnancy and might harm an unborn child. The contraception requirements for women participants of child-bearing potential might be a burden. Male participants will also be required to use contraception with female partners capable of becoming pregnant.
- The collection of sensitive or personal data will be undertaken only by staff trained in GCP and in the trial protocol.
- Participants will be informed of the results either at a seminar, or by email or on the phone. The PIS explains the hope to publish the results in medical journals, and present them at international conferences, and clarifies that participants will not be named in any of these or identified in any other way.
- Participants might believe that they are entitled to a share of potential future profits from commercialisation of the vaccine. The PIS explains that this is not the case.
- The confidentiality of participants' personal information is described in [Section 8.3.2](#).
- The trial has some medication restrictions which might be a burden: non-trial vaccines received within 28 days before or after any trial vaccination are not allowed (excepting flu vaccine – see Section 5.9.2); systemic immunosuppressive agents, such as a corticosteroid, may not be administered during the trial; dermal steroids are allowed but not if applied to the IM injection site.
- Based on other vaccines against different diseases, including those that use synthetic mRNA, the side effects are expected to be mild to moderate, short-lived reactions at the injection site such as discomfort, warmth, redness and swelling. Short-lived systemic symptoms such as fatigue, general malaise and headache are expected very commonly (more than 1 in 10 people). Less common reactions (expected in fewer than 1 in 10 people, but in more than 1 in 100) include chills, muscle pain, rash, and injection site itching.
- Rare reactions (less than 1 in 1,000 people, but more than 1 in 10,000) include enlarged lymph nodes, high fever ( $\geq 40$  °C), hypersensitivity (exaggerated reaction to the vaccine), urticaria (raised, itchy skin rash), and granuloma (area of inflammation in the skin) or sterile abscess (lump) at the injection site.
- Very rarely (less than 1 in 10,000 people) vaccines may cause convulsions with fever, drowsiness, and macrophagic myofasciitis (a rare muscle disease).

- Severe allergic reactions to vaccines are very rare (less than 1 in 10,000 people). However, appropriate medical treatment and trained staff will be available in case this occurs.
- The theoretical risk of ADE is discussed in [Section 1.2.4](#).

These risks will be carefully explained so that participants know what is involved and what to expect in the way of side effects.

Participants will be monitored closely during the trial, to identify as early as possible any problems so that they can be handled appropriately. They will be given 24-hour phone numbers in case they wish to speak to a doctor.

Because this is a first-in-human trial, there will be a dose escalation cohort with sentinel participants at each dose level, who will be vaccinated 2 days before any others. The dose escalation and evaluation plan for the first and second cohorts is detailed in Section 1.5.

The rules for pausing and discontinuing vaccinations in individuals and all participants in the trial have been clearly defined.

Participants will be paid for their time, inconvenience and travel expenses: £50 per scheduled visit, paid as a lump sum at the end of participation. This includes any travel expenses they might incur. Volunteers who attend screening but who are not enrolled will not receive payment. If their participation ends early, participants will be paid for the number of visits they've attended.

